### Main study endpoints:

Primary endpoint:

- Between- and within-subject variability (assessed by standard deviation) of mitoPO2 measurements over a period of 24 hours after ALA-induction.
  - o Initially in healthy volunteers
  - o Followed by neurosurgical patients admitted postoperatively to the ICU or MC.

Secondary endpoints:

- Description of the differences in the between- and within-subject variability between 3 hour offset ALA-patches.
- Description of between- and within-subject variability in healthy volunteers and neurosurgical patients in relation to the between- and within-subject variability of the INOX ICU-2 pilot study (P16.303)
- Report on adverse and serious adverse events of the mitoPO2 measurements.

**Study procedure:** MitoPO2 measurements will be taken in healthy volunteers using two ALA-patches offset to each other by 3 hours, this has been done to observe possible differences in measurements at different time-points after ALA-induction while maintaining other variables stable. Following the healthy volunteers, neurosurgical patients will be included. Patients will undergo neurosurgery as planned and common practice is that no major interventions are needed in the postoperative phase on the ICU/MC. At multiple predefined moments after surgery, mitoPO2 measurements will take place, again using two ALA-patches with a 3 hour offset.

**Nature and extent of the burden and risks associated with participation, benefit and group relatedness:** The risks are small in this study with no serious adverse events (SAE) known. The burden for participants is small since it involves a non-invasive measurement. We will perform this study first in health volunteers. Following the healthy volunteers, neurosurgical patients will be included. Patients will undergo neurosurgery as planned and common practice is that no major interventions are needed in the postoperative phase on the ICU. Normal clinical practice will continue and will not be altered. These patients will allow for the exploration of a possible effect of ICU admittance.

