### 2.2 Endpoint

In this descriptive study we aim to investigate mitoPO2's variability over the 24 hour period after ALA-induction

Specific objectives:

1. To describe the between- and within-subject variability (assessed by standard deviation) of mitoPO2 measurements over a period of 24 hours after ALA-induction.
  - a. Initially in healthy volunteers
  - b. Followed by neurosurgical patients admitted postoperatively to the ICU or MC.
2. To describe the between- and within-subject variability between 3 hour offset ALA-patches.
3. Description of between- and within-subject variability in healthy volunteers and neurosurgical patients in relation to the between- and within-subject variability of the INOX ICU-2 pilot study (P16.303).
4. Report on adverse and serious adverse events of the mitoPO2 measurements.

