## 7. Methods

### 7.1 Study procedures

#### 7.1.1 General

The study population will initially consist of healthy volunteers recruited via LUMC notice boards. Subjects will be interviewed prior to participation by a member of the research team, at which time information about the study will be provided and eligibility for participation will be determined based on the inclusion and exclusion criteria. Due to the 'off-label' use of the Alacare patches, specific information pertaining to its current use will be given. A written informed consent will be obtained from all volunteers. Upon inclusion further instructions for ALA-patch application will be provided along with alcohol wipes and 1 ALA-patch.

A self-adhesive ALA-patch will be applied parasternal and a second ALA-patch 3 hours later to rule out influence of the ALA-patch on the measurement variability, while keeping all other possible influencing variables the same. This offset of 3 hours was chosen since an increase in between- and within-subject variability was observed after 3 hours in the INOX ICU-2 pilot study. The course of mitoPO2 measurements will be measured at multiple predefined moments with several overlapping measurements. Subsequently, mitoPO2 measurements will be performed in neurosurgical ICU/MC at multiple predefined moments. This information will be used to further explore the increased variability in the critical care setting where it was first observed.

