## 9. Statistical analysis

### 9.1 Primary study outcome

The primary endpoint is the between- and within-subject variability of mitoPO2 measurements using the COMET measurement system at various moments during a 24 hour period with offset ALA-patches in healthy volunteers and neurosurgical ICU/MC patients to describe the variance mitoPO2 measurements and the effect of time-since-application of the ALA-patch and critical care interventions. Between-subject variability is defined as the variation of mitoPO2 at each measurement time point over the whole group. A mean of the mitoPO2 measurements and the standard deviation (SD) is calculated. This SD represents the between-subject variability. Within-subject variability is defined as the variation of mitoPO2 within one subject at each measurement time point. At each timepoint multiple measurements are taken. Since a mean mitoPO2 at each timepoint is used, the standard deviation (SD) of this measurement per participant is calculated. The mean of this SD of the study population represents the within-subject variability. These will be taken separately per ALA-patch.

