### 9.3 Statistical methods to be employed

Descriptive statistics will be used to describe the characteristics of the study population. The mitoPO2 at the different time points will be described with means, standard deviations (SD), medians and interquartile ranges (IQR) (Q1/Q3) as appropriate. For each time point, for each patient, a mean of 5 measurements of mitoPO2 is calculated with a corresponding SD. The mean of these standard deviations will be used to calculate the within-subject variability and the standard deviation of the overall mean per time-point will be used to calculate the between-subject variability.

Normality of variable distribution will be inspected using histograms. Assuming normal distribution of variables, the p values of a paired samples t-test will be reported for comparing overlapping measurement moments between patch 1 and patch 2. If variables are not normally distributed a Wilcoxon signed ranked test will be performed.

Signal quality of the mitoPO2 measurement will be described using the mean and SD of the signal quality. The statistical analysis will be conducted using the SPSS (Statistical Package for the Social Sciences) statistical package, release 23.0 (SPSS Inc., Chicago, IL) and STATA.

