## 14. Appendix 1: Results of the pilot study of the INOX ICU-2 study

**Table 1** The between-subject and within-subject variability of mitoPO2 per measurement moment. The within-subject variability is stable until 2 hours after transfusion, after which an increase is observed

| Measurement moment | Between-subject variability        |                                  | Within-subject variability                                      |
|--------------------|------------------------------------|----------------------------------|-----------------------------------------------------------------|
|                    | Mean mitoPO 2
(mmHg) | SD mitoPO 2
(mmHg) | Mean SD of mitoPO 2 per
measurement moment (mmHg) |
| Before RBC         | 70.5                               | 13.0                             | 3.0                                                             |
| At the end of RBC  | 68.1                               | 11.7                             | 3.4                                                             |
| 15 min after RBC   | 69.5                               | 17.7                             | 3.5                                                             |
| 30 min after RBC   | 68.4                               | 18.7                             | 5.8                                                             |
| 60 min after RBC   | 68.1                               | 15.8                             | 4.6                                                             |
| 120 min after RBC  | 70.0                               | 20.4                             | 3.6                                                             |
| 180 min after RBC  | 67.5                               | 28.2                             | 7.3                                                             |
| 24 hours after RBC | 90.0                               | 42.5                             | 8.7                                                             |

**Fig. 1** Course of mitoPO2 (mmHg) per subject during the measurements. Up to the first hour of measurements the between-subject variability seems stable, afterwards this variability of mitoPO2 increases

[figure not shown]

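### The only test for the two patches has no named variable; read naturally it compares mitoPO2 levels, and on no reading does it address between-subject SD

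*Protocol*

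**What the plan says.** The Summary lists as a secondary endpoint: "Description of the differences in the between- and within-subject variability between 3 hour offset ALA-patches". Section 2.2 repeats it as a specific objective. Section 7.1.1 (General) explains why a second patch is applied three hours after the first: "to rule out influence of the ALA-patch on the measurement variability", with other influences held the same.

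Section 9.1 defines the two quantities. Between-subject variability is the SD across subjects at a time point. Within-subject variability is an average of per-subject SDs: "The mean of this SD of the study population represents the within-subject variability". Both are to be taken separately for each patch.

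Section 9.3 says that for each patient and time point a mean of five readings "is calculated with a corresponding SD". It then gives the only test in the section: "the p values of a paired samples t-test will be reported for comparing overlapping measurement moments between patch 1 and patch 2". The fallback is: "If variables are not normally distributed a Wilcoxon signed ranked test will be performed". Neither sentence says whether the tested variable is the subject's mean or the subject's SD.

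**The concern.** A paired t-test and a Wilcoxon signed-rank test both ask whether paired differences are centred on zero. Applied to mitoPO2 values at the same clock time under an older and a newer patch, they ask whether the level differs. The study was prompted by a change in spread. The pilot table in Appendix 1 is captioned: "The within-subject variability is stable until 2 hours after transfusion, after which an increase is observed".

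If the test is run on levels, its p values could be unremarkable even if patch age were the whole cause of the extra variability. A small p value could equally reflect a level shift that says nothing about variability. As these are the only p values planned for the patch comparison, readers are likely to take them as its result.

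**Working it through.** **1. The plan's own figure.** Section 4.4 uses n = (σ(1.96 + 1.28)/(μ − μ0))² with σ = 5.67, μ = 8.7 and μ0 = 4 mmHg. This gives (5.67 × 3.24/4.7)² = 15.28, stated as 15, and 15 × 1.1 = 16.5, stated as 17. The figure reproduces. The quantity in that formula is the per-subject SD, so the protocol already treats it as an analysis variable. I use n = 15 completers below.

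**2. What is paired.** From Table 2 in section 7.2.1, the patches overlap at four moments (hours after the 4-hour induction, patch 1 against patch 2): 3 v 0, 6 v 3, 24 v 21 and 27 v 24.

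**3. Pilot values (Appendix 1, Table 1), mmHg.**

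| Moment | Mean | Between-subject SD | Within-subject SD |
|---|---|---|---|
| Before RBC | 70.5 | 13.0 | 3.0 |
| 120 min | 70.0 | 20.4 | 3.6 |
| 180 min | 67.5 | 28.2 | 7.3 |
| 24 hours | 90.0 | 42.5 | 8.7 |

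From baseline to 180 min the mean moved by 3.0 mmHg, while the SDs rose by factors of 28.2/13.0 = 2.2 and 7.3/3.0 = 2.4. This is the closest pilot contrast to the first overlap, though pilot times count from transfusion, not from induction.

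**4. Test on levels.** Let X and Y be a subject's means under the two patches, with equal expectations. Then X − Y has expectation zero whatever the two SDs are. For normal data the paired t statistic keeps its null distribution, so the rejection rate is 5%. In simulation with SDs of 28.2 v 13.0 and 28.2 v 20.4, n = 15 and patch correlation 0.3 to 0.7, it was 4.6 to 5.6%.

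**5. Test on per-subject SDs.** Take true within-subject SDs averaging 7.3 v 3.6, varying by 50% between subjects, correlation 0.5 between patches, five readings each and n = 15. A paired t-test on log SD then rejects in about 92% of trials. With no correlation between the patches I get about 83%. For 7.3 v 3.0 at n = 15 to 17, paired tests on raw SDs reject in 93 to 100%.

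**6. Between-subject SD.** There is one value per patch and moment in each group, so there are no per-subject differences to test. The Pitman-Morgan test uses the correlation of X + Y with X − Y:

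r = (σ1² − σ2²)/√[(σ1² + σ2²)² − 4ρ²σ1²σ2²]

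Approximate power at n = 15 is Φ(atanh(r)·√12 − 1.96). With ρ = 0.5:

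- 28.2 v 13.0: r = 626.24/891.83 = 0.702, atanh(r) = 0.872, × √12 = 3.02, power about 0.86. Simulation gives 88%, and 82 to 95% for ρ from 0.3 to 0.7.
- 28.2 v 20.4: r = 379.08/1066.09 = 0.356, atanh(r) = 0.372, × √12 = 1.29, power about 0.25. Simulation gives 26%, and 22 to 36% over the same ρ.

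The patch correlation and the 50% spread of subject SDs are assumptions; the protocol gives neither.

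**The case against.** The strongest reply is that section 9.3 never says the test is on mean mitoPO2. It has just defined a per-subject SD, and section 4.4 already uses that SD as a variable. A paired t-test on it is a valid test of within-subject variability. This stands. A reader might infer that the planned test cannot answer the variability question at all; the text does not support that for the within-subject half, because the variable is left open.

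Second, the endpoint is a description. Section 2.2 opens with "In this descriptive study we aim to investigate", and section 9.1 has both SDs taken per patch, so a change in spread would show in the tables. This also stands. A reader might infer that the study would report no difference between patches; that overlooks the described SDs.

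Third, one might read section 7.1.1 as promising to declare the patch without influence if p exceeds 0.05. It does not. The phrase about ruling out influence explains the two-patch design, and no such decision rule appears anywhere.

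Fourth, the pilot mean does not stay flat: it is 90.0 mmHg at 24 hours, and two of the four overlaps fall late. A comparison of levels is therefore not pointless there, but it still concerns level.

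Finally, the exact test variable might be left to a statistical analysis plan. That would answer a complaint about missing detail. It does not answer the fact that the one test the protocol names fits only part of the endpoint at best, and its natural reading fits none of it.

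**Conclusion.** The point holds in a limited form. Section 9.3 should name the variable. Read naturally as mitoPO2 values, the paired test has only its 5% false-positive rate against a change in spread at equal means, so its p values would not bear on the patch endpoint. Read as per-subject SDs, it is sound for within-subject variability. On neither reading does it address between-subject SD.

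The 5% follows from the test's construction for normal data and does not depend on the assumed correlation. The power figures for the alternatives do depend on the assumed correlation and spread of SDs. They show that the planned size can detect contrasts as large as the pilot's from baseline to 180 min, but has little power for a moderate ratio of between-subject SDs such as 28.2 v 20.4.

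**What to change.** In section 9.3, state that at each overlapping moment:

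- (a) the paired test is on each subject's SD of the five readings, preferably on the log scale, reported as a ratio with 95% CI;
- (b) between-subject SDs are compared by their ratio with a 95% CI for paired variances (Pitman-Morgan), with a note that power is limited for moderate ratios, or are declared descriptive only;
- (c) any paired test of mean mitoPO2 is a supportive check of level.

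Add that any statement that the patch has no effect on variability rests on the intervals in (a) and (b), not on a non-significant p value for level.

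The cost is a few lines of text. The five readings per patch and moment are already collected, so no further data or participants are needed.

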## **10. Ethical considerations**

### **10.1 Regulation Statement**

The study will be conducted according to the principles of the Declaration of Helsinki (accepted by the WMA General Assembly, October 2013, Fortaleza, Brazil) and in accordance with the Medical Research Involving Human Subjects Act (WMO).

### **10.2 Recruitment and Consent**

The protocol of this study will be submitted to the Medical Ethics Committee of the Leiden- Den Haag-Delft. The study will not commence before formal approval has been granted.

The study population consists of patients undergoing elective surgery. Patients admitted to the neurosurgical department which will be admitted to the ICU or MC post-operatively, will be asked for an informed consent on the day before the neurosurgical operation. An information leaflet will be given and informed consent will be sought. Patients or their legal representatives will be told that a person can only participate in the study if he/she meets the inclusion criteria. If written informed consent is given the self-adhesive ALA-patch will be placed in the preoperative phase. The induction time of PpIX is at least 4 hours, therefore the first measurements will be taken postoperatively. After inclusion of a patient meeting the eligibility criteria, each patient will be assigned a unique study number.

### **10.3 Objection by minors or incapacitated subjects**

Section 4, subsection 2, of the WMO stipulates that a legally incompetent adult cannot be forced to undergo a treatment or behave in a particular manner in the context of non-therapeutic research against his or her will. Subjects younger than 18 years are already excluded from the study. We don't expect patients that are not capable for the informed consent procedure. If there are adults, that are incapable of giving informed consent, a legal representative will be asked to give informed consent according to the GCP guideline. When the subject is able to give informed consent after being included in the study by consent of the legal representative and denies any further participation, the subject will be excluded from the study without any consequences. The data collected up to that point will be used for analysis. No additional data will be collected.

### **10.4 Benefits and risk assessment, group relatedness**

The proposed study aims to describe the between- and within-subject variability of mitoPO2 measurements. The measurements necessary to assess the defined study endpoints are not expected to negatively influence the result of treatment.

### 10.5 Compensation for injury

The Leiden University Medical Centre has a liability insurance which is in accordance with article 7, subsection 6 of the WMO.

The LUMC (also) has an insurance which is in accordance with the legal requirements in the Netherlands (Article 7 WMO and the Measure regarding Compulsory Insurance for Clinical Research in Humans of 23th June 2003). This insurance provides cover for damage to research subjects through injury or death caused by the study.

1. € 650.000, -- (six hundred and fifty thousand Euro) for death or injury for each subject who participates in the Research;
2. € 5.000.000, -- (five million Euro) for death or injury for all subjects who participate in the Research;
3. € 7.500.000, -- (seven million and five hundred thousand Euro) for the total damage incurred by the organization for all damage disclosed by scientific research for the Sponsor as 'verrichter' in the meaning of said Act in each year of insurance coverage.

The insurance applies to the damage that becomes apparent during the study or within 4 years after the end of the study.

## 11. Administrative Aspects and Publication

### 11.1 Handling and storage of data and documents

All patients will be addressed to with a random patient identification code, which will be generated by CASTOR EDC, the electronic case report form. The codebook will be stored digitally, outside the investigator site file folder, with restricted access. Only the research team, monitor, and IGJ will have access to this folder. The code will be safeguarded by the coordinating investigator. The codebook will be encrypted with a password. All data will be stored for further publication. All handling of personal data will comply with the EU General Data Protection Regulation (GDPR) and the Dutch Act on Implementation of the General Data Protection Regulation (in Dutch: Uitvoeringswet AVG). Data will be stored for 20 years at the research location. Source data on the COMET device will be anonymous, it only contains date and time of measurement, it is not possible to enter patient name, personal number or date of birth. The COMET can only retrieve the data of the current/most recent measurement series until the user selects a new series or measurement spot. To store COMET data, it will be downloaded via an USB memory onto a computer memory conforming to the institution's privacy guidelines and the USB memory will be erased. The COMET data will be shared anonymously with the manufacturer.

### 11.2 Monitoring and Quality assurance

The risks associated with this study are moderate for the subjects (more information can be found in appendix 3). Therefore, only on-site monitoring is needed, which will happen in accordance of the NFU guideline of monitoring. Being labelled as a moderate risk study, the monitoring will be moderate to ensure the integrity and safety of the study participants. The monitor pool of Leiden University Medical Center, which are qualified for monitoring, will monitor this study. The monitor pool is an independent group of data managers or research nurses, who aren't involved in the study in any way other than monitoring. They will report to the principal investigator and to the coordinating investigator. The head of department will be notified by the monitor, when the monitor notices frequent or substantial omissions.

### 11.3 Amendments

Amendments are changes made to the research after a favourable opinion by the accredited METC has been given. All amendments will be notified to the METC that gave a favourable opinion. A 'substantial amendment' is defined as an amendment to the terms of the METC application, or to the protocol or any other supporting documentation, that is likely to affect to a significant degree:

- the safety or physical or mental integrity of the subjects of the trial;
- the scientific value of the trial;
- the conduct or management of the trial; or
- the quality or safety of any intervention used in the trial.

All substantial amendments will be notified to the METC and to the competent authority. Non-substantial amendments will not be notified to the accredited METC and the competent authority, but will be recorded and filed by the sponsor.

#### **11.4 Annual progress report**

The investigator will submit a summary of the progress of the trial to the accredited METC once a year. Information will be provided on the date of inclusion of the first subject, numbers of subjects included and numbers of subjects that have completed the trial, unexpected problems and amendments.

